### Confidentiality {27}

Each study participant will receive a 5-digit alphanumeric unique study ID. From the app, deidentified anonymised data will be stored in Excel. This will be stored confidentially before, during, and after the trial.

### Provisions, if any, for ancillary and post-trial care, and for compensation to those who suffer harm from trial participation {30}

This is a non-pharmacological intervention; therefore, there are no specific post-trial care provisions.

## Discussion

Existing research on cardiometabolic multimorbidity (CMM) has largely been disease-centric, leaving gaps in understanding the comprehensive landscape of multi-condition management. The Shraddha lifestyle toolkit addresses this gap by providing a culturally tailored, multi-component lifestyle intervention for individuals with CMM. Its distinctiveness lies in evaluating the implementation of the *combined* effect of diet, physical activity, stress management, tobacco and alcohol cessation, and medication adherence on clinical, behavioural, and intergenerational outcomes through a cluster randomised controlled trial.

Despite the growing burden of CMM in India, research remains limited, mostly relying on secondary data [25, 27]. Global studies have linked CMM to adverse outcomes, including impaired quality of life, increased mortality, and functional decline [26, 28–31]. Prevalence estimates vary widely: 33.1% among women ≥45 years in China [38]; 8.9% in Brazil, with high rates of diabetes, stroke, and myocardial infarction [39]; and 3.5% among Canadians ≥50 years, with strong associations to inactivity and stress [29]. The intergenerational dimension is highlighted in longitudinal studies, demonstrating how early-life exposures and parental health shape offspring cardiovascular trajectories [40].

The Theory of Change (ToC) underpins the design of this protocol. The intervention assumes that structured, culturally adapted lifestyle counselling, delivered by community health workers and reinforced via mHealth support, will increase awareness, motivation, and adoption of healthy behaviours. These proximal changes are expected to improve intermediate outcomes—HbA1c, blood pressure, BMI, and medication adherence—which, over time, will lead to long-term impacts including reduced morbidity and mortality, improved quality of life, and intergenerational risk reduction. Capacity-building for frontline workers ensures sustainability, while family engagement and digital reinforcement strengthen adherence and scalability.

Current evidence supports the effectiveness of individual lifestyle interventions for diabetes, hypertension, and heart disease. The logical extension to a comprehensive toolkit addresses the shared pathways of CMM and aligns with national NCD policies, WHO ‘Best Buys’ [41], and SDGs 3.4, 3.5, and 3.8 [42]. By explicitly incorporating the intergenerational dimension, the study addresses a critical gap in existing research, exploring how family-centric interventions can interrupt the cycle of CMM risk.

Furthermore, the protocol’s design integrates implementation science principles, evaluating both clinical and process outcomes (acceptability, adoption, fidelity, coverage, cost). The ToC framework enables mapping of each intervention component to expected outputs and outcomes, guiding continuous iteration and adaptation. This ensures that the intervention is not only effective in clinical terms but also feasible, scalable, and sustainable within India’s health system.

In conclusion, by linking a novel multi-component lifestyle intervention to a clear Theory of Change, this study advances both the evidence base and implementation strategy for managing CMM. It has the potential to inform scalable, culturally appropriate, and intergenerationally mindful interventions for cardiometabolic health in India and other LMICs (Table 3).

**Table 3 Tab3:** Outcome measures and tools for measurements

Outcome	Outcome measure
Diet and nutrition^a^	FFQ, app-based calorie estimation
Physical activity^b^	G-PAQ
Alcohol and tobacco use^c^	WHO-ASSIST
Adherence to drugs^d^	MMAS-8
Mental stress^e^	PSS-10
Adverse events	Death, revascularisation, rehospitalisation, reinfarction
Quality of life^f^	EQ-5D-L3
Laboratory outcomes	HbA1C
Anthropometric	Weight, BMI
Service user satisfaction^g^	PSQ 18
Resource utilisation	Intervention and treatment-related costs
Acceptability/adoption/appropriateness	Qualitative measures

^a^Cade JE, Burley VJ, Warm DL, Thompson RL, Margetts BM. Food-frequency questionnaires: a review of their design, validation and utilisation. *Nutrition Research Reviews*. 2004 Jun;17(1):5–22

^b^Sember V, Meh K, Sorić M, Starc G, Rocha P, Jurak G. Validity and reliability of international physical activity questionnaires for adults across EU countries: systematic review and meta analysis. *International Journal of Environmental Research and Public Health*. 2020 Oct;17(19):7161

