### Sample size {14}

The sample size was determined using computer-generated randomisation at the cluster level across 18 sub-centres (9 intervention and 9 control).

As this is a type III implementation study, the primary focus will be on evaluating implementation outcomes. In addition, effectiveness will also be assessed based on the following sample size estimation.

To detect a minimum clinically meaningful difference of 0.5% in HbA1c between the two groups, with 80% power, a two-sided alpha of 0.05, and assuming a standard deviation of 1.5% [33], the required sample size under individual randomisation was calculated to be 142 participants per arm.

Given the cluster design, with a planned cluster size of 90 participants and an intracluster correlation coefficient (ICC) assumed to be 0.05, the design effect was calculated as 5.45 using the formula DE = 1 + (m − 1) × ICC. After adjusting for clustering, the required sample size was 774 participants per arm.

The trial will include nine clusters per arm, with 90 participants per cluster (810 participants per arm), which exceeds the minimum required sample size. The fixed cluster size and number of clusters are determined by the structure of the ENDIRA cohort, within which this follow-up study is embedded.

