### Eligibility criteria for participants {10}

Inclusion criteria: individuals diagnosed with CMM (defined as the presence of two or more of the following conditions: diabetes mellitus, hypertension, stroke, or coronary heart disease); stroke would include a documented ischaemic or haemorrhagic cerebrovascular accident as diagnosed from symptoms or imaging studies; coronary heart disease as defined by individuals with a history of an acute coronary syndrome, or diagnosed coronary artery disease defined as 50% stenosis of one or more of the epicardial coronaries on CT or conventional coronary angiography; or wall motion abnormalities (WMA) on echocardiography or nuclear imaging suggestive of an old myocardial infarction; age ≥ 18 years, providing informed consent for participation and agreeing to follow-up.

Exclusion criteria: individuals with cognitive impairment who are unable to carry out instructions; bedridden individuals; individuals with other significant confounding health conditions additionally like malignancy or chronic airway disease; individuals ≥75 years of age; individuals with a terminal medical condition; pregnant or lactating mothers.

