The Health Belief Model (HBM) serves as the conceptual framework for our study. HBM provides a structured understanding of how patient beliefs and perceptions influence their health behaviours and how the intervention can modify these beliefs to promote better health outcomes. The Shraddha lifestyle intervention is grounded in six core HBM constructs:Perceived susceptibility: Patients of CMM need to understand that they are at a higher risk of recurrence of adverse events such as myocardial infarction, heart failure, or stroke. The Shraddha website will deliver educational broadcasts that highlight the risks associated with poor control of metabolic parameters fostering a sense of urgency for lifestyle changes and adherence to prescribed medications.Perceived severity: If patients believe that the consequences of unmanaged diabetes or hypertension are severe, they may be more likely to engage in preventive behaviours. The Shraddha website will provide videos that illustrate the potential sequences of uncontrolled blood sugar and BP, such as renal failure, vision loss, or cardiovascular events, making the risks more tangible and relatable.Perceived benefits: Success stories and real-life examples of reduced HbA1c levels, BP, and BMI will be shared with participants to reinforce the tangible benefits of their actions. Participants will be able to track improvements in their health indicators (e.g. HbA1c levels, BP, BMI), reinforcing the perceived benefits of the intervention.Perceived barriers: Barriers may include lack of time, difficulty in accessing healthy foods, unavailability of walkways, paths, or fear of side effects from medications. The Shraddha website will provide practical, culturally tailored solutions such as meal plans and simple physical activity suggestions that can be done at home. ASHA workers will offer support during periodic home visits to address any concerns.Cues to action: Reminders and alarms will serve as cues to action, prompting participants to take medications, engage in physical activity, maintain a balanced diet, and avoid tobacco and alcohol.Self-efficacy: The Shraddha website will include features that allow patients to set achievable short-term goals (e.g. taking a 10-min walk each day or avoiding sugar in one meal), track their progress, and receive rewards or recognition for their efforts.

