### Harms: definition and assessment {22}

As this study is implementation of a lifestyle toolkit, no adverse events or serious adverse events and harms from the intervention are anticipated. But if there are any, they will be reported to relevant regulatory bodies such as Project Management Group, Trial Steering Committee, District Health Authority, and Ethics Committee. Trial deviations will be reported to the ethical committee.

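### The adverse-event list in Table 3 does not fit the population admitted: stroke and first infarction have no category, and a first admission is ambiguous

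*Protocol article*

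**What the plan says.** The only list of clinical events is the adverse-events row of Table 3, placed in the Discussion of the protocol article: "Death, revascularisation, rehospitalisation, reinfarction". None of the four terms is defined there or elsewhere in the article.

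The section Eligibility criteria for participants {10} sets the population. Cardiometabolic multimorbidity is "defined as the presence of two or more of the following conditions: diabetes mellitus, hypertension, stroke, or coronary heart disease". Coronary heart disease may be established by an acute coronary syndrome, by imaging signs of an old infarction, or by "diagnosed coronary artery disease defined as 50% stenosis of one or more of the epicardial coronaries on CT or conventional coronary angiography". The remaining inclusion conditions are "age ≥ 18 years, providing informed consent for participation and agreeing to follow-up". An earlier hospital admission is not among them.

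Under Patient and public involvement, the Health Belief Model text says that these patients are at "higher risk of recurrence of adverse events such as myocardial infarction, heart failure, or stroke".

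Harms: definition and assessment {22} states that "no adverse events or serious adverse events and harms from the intervention are anticipated", and that any which do occur will be reported to the oversight bodies. It defines no events.

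**The concern.** The terms reinfarction and rehospitalisation suit a cohort recruited after an infarct. This trial recruits on any two of four conditions, and many qualifying histories contain no infarct. For such a participant an infarction during follow-up is a first infarction, which the list does not name. A stroke, first or recurrent, is not named for anyone, although stroke defines part of the population and the protocol itself cites it as a risk.

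What is at stake is the meaning of the event counts. If the terms are applied literally, whether an infarction can be counted depends on the participant's history at entry. If they are applied loosely, the result depends on how each data collector reads an undefined word. The endline survey is done at the household by ASHA workers, and the article blinds only the data analysts, so a loosely worded field leaves room for recording to differ between clusters or arms.

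**Working it through.** **What the trial is sized on.** The only sample size calculation concerns HbA1c. Its inputs are a difference of 0.5%, "with 80% power, a two-sided alpha of 0.05, and assuming a standard deviation of 1.5"%.

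- Per arm under individual randomisation: n = 2 × (1.960 + 0.842)² × 1.5² / 0.5² = 2 × 7.849 × 9 = 141.3, rounded up to 142. This matches the plan.
- Clustering: "the design effect was calculated as 5.45 using the formula DE = 1 + (m − 1) × ICC", that is 1 + 89 × 0.05 = 5.45. Then 142 × 5.45 = 773.9, rounded up to 774. This also matches.
- Planned: 9 × 90 = 810 per arm.

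These figures reproduce, and none of them involves clinical events. The point below therefore leaves the sample size untouched.

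**The event list against the entry criteria.** Taking the Table 3 terms literally for histories that the eligibility section admits:

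| History at entry | Infarction in follow-up | Stroke in follow-up | Admission in follow-up |
|---|---|---|---|
| Diabetes + hypertension | First infarction: no category | No category | Unclear if never admitted before |
| Stroke + hypertension | First infarction: no category | No category | Unclear if never admitted before |
| Coronary disease by stenosis only + diabetes | First infarction: no category | No category | Unclear if never admitted before |
| Prior infarct + diabetes | Counts as reinfarction | No category | Counts if admitted before |

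Death and revascularisation need no earlier event and count in every row.

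**Whether another section widens the list.**

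- The participant timeline {13} has no row for clinical events.
- The effectiveness row of Table 2 names questionnaires, blood pressure, HbA1c and BMI, and no clinical events.
- The harms section {22} gives a reporting route but no definitions.

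Table 3 is therefore the only statement of which events are recorded.

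**How many events are affected.** This would need the share of participants without a prior infarct, the rates of first and recurrent infarction, and the stroke rate. The document gives none of them, so no number follows.

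**The case against.** The strongest case on the other side has five parts.

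1. *The list is wider than the two awkward terms.* This stands. Death and revascularisation are also listed, and neither depends on history.
2. *Rehospitalisation may simply mean any admission after enrolment.* This stands as a possibility. On that reading, first infarctions and strokes that lead to admission would be captured, though not identified as infarction or stroke. The term is undefined, so neither reading can be ruled out.
3. *Table 3 is a short summary in a condensed article.* Operational definitions may well sit in the full protocol or the case report form, and their absence here is not the complaint. The complaint is that the terms that are stated do not match the population that is stated.
4. *Recruitment is mostly of cardiac patients.* The trial setting section describes 2064 people with documented cardiovascular disease, and the consent section on specimens {26b} speaks of cardiac patients with type 2 diabetes. This may explain the wording and would reduce the number affected. It does not remove the mismatch, because patients with stroke or with stenosis only need not have had an infarct.
5. *The Health Belief Model passage describes educational content and speaks of recurrence.* That is fair. It is supporting evidence only; the mismatch between Table 3 and the eligibility section does not need it.

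A reader might also infer that the trial is blind to the main cardiovascular events, that strokes would go unreported as harms, or that chance imbalance in prior infarct would bias a comparison of event rates. The document supports none of these. Such events may enter as deaths, revascularisations or admissions. The harms section does not tie reporting to Table 3. No between-arm analysis of clinical events is described: the statistical analysis section covers blood pressure, glycaemia, quality of life and implementation measures.

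**Conclusion.** The mismatch is real and limited. As written, any stroke and any first infarction lack a category of their own, and the status of a first admission is ambiguous. This follows directly from the Table 3 row and the entry criteria, and needs no assumption about rates.

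It affects a clinical-event and safety outcome. The primary outcomes are implementation outcomes and the sample size rests on HbA1c, so neither is touched.

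No size can be put on it. A percentage of missed infarctions could be produced by assuming infarct rates and a share without prior infarct, but it would only reflect those assumptions. Counting the qualifying combinations without coronary disease (4 of 11) is no substitute, because it counts combinations and not participants. The wording should be corrected before events are recorded; nothing here shows that the trial's main conclusions are at risk.

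**What to change.** Replace the adverse-events entry in Table 3, and the matching fields on the tablet form, with:

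- death from any cause;
- any myocardial infarction, first or recurrent;
- any stroke, first or recurrent;
- any revascularisation;
- any hospitalisation after enrolment.

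Record these identically in both arms. This brings Table 3 into line with the eligibility section and with the risks named under the Health Belief Model.

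The cost is one reworded table row and a few more form fields, with no extra visit. Reporting the events by infarct or stroke history is not required.

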Role of trial sponsor and funders in design, conduct, analysis, and reporting of trial; including any authority over these activities {5c}	Study sponsor does not have any role in the collection, management, analysis, and interpretation of data
Composition, roles, and responsibilities of the coordinating site, steering committee, endpoint adjudication committee, data management team, and other individuals or groups overseeing the trial, if applicable {5d}	Not applicable
Protocol and statistical analysis plan	
Where the trial protocol and statistical analysis plan can be accessed	Can be accessed in the CTRI website
Data sharing	
Where and how the individual deidentified participant data (including data dictionary), statistical code, and any other materials will be accessible {29}	Deidentified participant data will be shared on an individual request basis
Conflicts of interest	
Financial and other conflicts of interest for principal investigators and steering committee members {7b}	The authors declare that there are no competing interests
Dissemination policy	
Plans to communicate trial results to participants, healthcare professionals, the public, and other relevant groups (e.g. reporting in trial registry, plain language summary, publication) {31}	The results will be shared through peer-reviewed publication, the public and research community, and policy makers

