### Participant timeline {13}

**Table Tabb:** 

Timepoint	Trial period				
	Enrolment		Post-randomisation		Close-out
	(−ti to 0)	0	t1 (6 mo)	t2 (12 mo)	tx
Enrolment					
Eligibility screen	X				
Informed consent	X				
Baseline demographics	X				
Cluster randomisation (sub-centres: arm A/arm B)		X			
Intervention/comparator					
Shraddha lifestyle toolkit (arm A)		X			X
Standard of care (arm B)		X	X	X	X
Assessments					
Clinical measures (BP, weight, BMI)	X		X	X	X
Laboratory (HbA1c)	X		X	X	X
Diet (FFQ/calorie tracking)	X		X	X	X
Physical activity (GPAQ)	X		X	X	X
Substance use (WHO-ASSIST)	X		X	X	X
Medication adherence (MMAS-8)	X		X	X	X
Mental stress (PSS-10)	X		X	X	X
Quality of life (EQ-5D-L3)	X		X	X	X
Implementation outcomes (acceptability, adoption, appropriateness, fidelity, cost effectiveness)			X	X	X

Baseline = 0; t1 = 6 months (midline); t2 = 12 months (endline). The arrow indicates continuous delivery of the Shraddha lifestyle toolkit (mHealth messages, JAK visits, yoga sessions) from allocation to endline. Protocol v4 (26 September 2025); IEC ASM-AIMS ECASM-AIMS-2024-001; CTRI/2025/08/092529

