### Data collection methods {18a}

Data will be collected at household (demographic data, data collected using standardised tools/questionnaires), by ASHA workers, and will be entered into a tablet PC. Before starting data collection, all research staff will be trained in the protection of human subjects, good clinical practice guidelines and administration, data entry, and analysis of study-specific data collection tools.

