#### Study duration and follow-up

The study will be of 24 months including 12 months of intervention, and outcomes will be measured at baseline 6 and 12 months for primary and secondary outcomes.

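### Table 3 lists clinical events as an outcome, but the visit schedule and harms section do not provide for collecting them, which leaves a risk of incomplete and unequal ascertainment

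*Protocol article*

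**What the plan says.** Four parts of the protocol article bear on this.

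- **Table 3 (Discussion)** has an adverse-events row that reads "Death, revascularisation, rehospitalisation, reinfarction". Most other rows name an instrument. This one names event types only, with no source and no timepoint.
- **Participant timeline {13}** has rows for blood pressure, weight and BMI, HbA1c, diet, physical activity, substance use, medication adherence, stress and quality of life. The last row begins "Implementation outcomes (acceptability, adoption, appropriateness, fidelity, cost effectiveness". There is no row for death, admission, revascularisation or reinfarction.
- **Harms {22}** states that "no adverse events or serious adverse events and harms from the intervention are anticipated", and continues: "But if there are any, they will be reported to relevant regulatory bodies". The recipients are named as "Project Management Group, Trial Steering Committee, District Health Authority, and Ethics Committee".
- **Administrative information, item {5d}**, whose prompt covers "Composition, roles, and responsibilities of the coordinating site, steering committee, endpoint adjudication committee, data management team", is answered as not applicable.

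Three more general statements could be read as covering events. Study duration and follow-up says that "outcomes will be measured at baseline 6 and 12 months for primary and secondary outcomes". Data collection methods {18a} says "Data will be collected at household (demographic data, data collected using standardised tools/questionnaires), by ASHA workers". Item {26b} says that consent to review medical records will be sought. None of the three names clinical events.

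**The concern.** An outcome that is listed but given no collection procedure tends to be recorded only when someone happens to report it. That matters more here than in many trials, for two reasons. First, only the data analysts are blinded. Second, the intervention arm has extra occasions on which an event could come to staff attention: the two-way app with uploads and queries, the monthly village meetings intended to retain intervention participants, and the toolkit visits and yoga sessions.

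Three things are at stake:

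- whether any table of events by arm can be read as a comparison;
- whether the trial can make a sound safety statement about people with established coronary disease or stroke who are encouraged to be physically active;
- whether deaths and admissions are known well enough to support the treatment-cost outcome and to explain losses to follow-up.

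A smaller inconsistency sits beside this. Harms are to go to a steering committee, while the item that would describe such a committee is marked as not applicable.

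**Working it through.** **Step 1. Set Table 3 against the timeline.**

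- Diet, physical activity, alcohol and tobacco, adherence, stress, quality of life, HbA1c, and weight/BMI: each has a timeline row at baseline, 6 and 12 months.
- Acceptability, adoption and appropriateness: covered by the implementation row at 6 and 12 months.
- Resource utilisation: no row of its own, although cost effectiveness appears in the implementation row.
- Service user satisfaction (PSQ-18): no row.
- Death, revascularisation, rehospitalisation, reinfarction: no row.

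The omission is therefore real but not confined to events. The timeline is not a complete list of what Table 3 promises.

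**Step 2. Look for a procedure elsewhere.** The harms section gives no definition, no solicited question and no timing. The description of household data collection extends to demographic data and standardised tools or questionnaires. The record-review consent is not tied to event ascertainment or to a visit. No passage supplies the missing procedure.

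**Step 3. Check the plan's own figures.** The article gives no figure for events. Its HbA1c sample size reproduces:

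- n per arm = 2 × (1.96 + 0.8416)² × 1.5² / 0.5² = 141.3, rounded up to 142.
- Design effect = 1 + (90 − 1) × 0.05 = 5.45.
- 142 × 5.45 = 773.9, rounded up to 774. Planned: 9 × 90 = 810 per arm.

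Nothing in this point changes those figures.

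**Step 4. Illustrate what unequal capture would do.** The article gives neither an event risk nor a capture rate, so both are assumptions here. Let p be the true 12-month risk, equal in both arms, and let s_A and s_B be the proportions of events captured in the intervention and control arms.

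Recorded events per arm = 810 × p × s. Apparent risk ratio = (p × s_A) / (p × s_B) = s_A / s_B, so p cancels.

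With p = 10% (81 true events per arm):

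| s_A | s_B | Recorded A | Recorded B | Apparent ratio |
|---|---|---|---|---|
| 90% | 90% | 72.9 | 72.9 | 1.00 |
| 90% | 80% | 72.9 | 64.8 | 1.125 |
| 90% | 70% | 72.9 | 56.7 | 1.29 |
| 90% | 60% | 72.9 | 48.6 | 1.50 |
| 70% | 90% | 56.7 | 72.9 | 0.78 |

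At p = 5% the counts for 90% against 60% are 36.5 and 24.3. At p = 15% they are 109.4 and 72.9. The ratio is 1.50 in both cases.

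Equal capture removes the bias in the ratio but not the loss of events. At 70% capture in both arms the ratio is 1.00, while 81 × 0.30 = 24.3 events per arm go unrecorded.

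**The case against.** The other side has several good points.

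- **Symmetric capture is possible.** Outcomes in general are said to be measured at baseline, 6 and 12 months. The ASHA household surveys are described without any difference by arm, and record review is foreseen. A household survey at 12 months would ordinarily reveal a death in either arm. This stands, and it rules out saying that events can surface only through toolkit contact.
- **A missing row is not proof of non-collection.** PSQ-18 is missing from the timeline too, and case-report detail is often left to a full protocol. This stands in part. However, the article answers the schedule, harms and oversight items explicitly, and those answers do not fit Table 3.
- **The harms section concerns harms from the intervention.** It does not say that it replaces collection of the Table 3 outcomes. True, but no other section supplies the collection.
- **No formal event comparison is stated.** Objective 4 and the statistical analysis section name no clinical events, and implementation outcomes are primary. This lowers the stakes to descriptive and safety reporting.
- **The ratios restate their assumptions.** They do, and they are shown only as an illustration.

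A reader might go further and infer that events would be captured more often in the intervention arm, making the toolkit look harmful. The documents do not support that. They give no capture rates, and unblinded staff could also under-report in the intervention arm. Nor can it be said that controls have no JAK contact. Every cluster is a JAK sub-centre, control clusters continue usual care, and the monitoring section describes monthly ward-level meetings without restriction by arm. Only the toolkit contact differs.

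A reader might also take the lack of a separate stroke item as an error. Admitted or fatal strokes already fall under rehospitalisation or death, so a separate item is a refinement.

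**Conclusion.** The point holds as an inconsistency with a credible risk attached. Table 3 lists clinical events as an outcome, the timeline does not schedule them, the harms section relies on reporting if they arise, and the general statements do not name them. With an open-label design and extra toolkit contact in one arm, this leaves room for incomplete and unequal ascertainment.

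The size and direction of any imbalance cannot be determined from the documents. The illustrative ratios include 1.00 under equal capture and fall on either side of it otherwise. They depend wholly on the assumed capture proportions. The HbA1c sample size, the primary implementation outcomes and the planned models for blood pressure, glycaemia and quality of life are not affected. The mismatch between the harms section and item {5d} is minor but should be settled at the same time.

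**What to change.** 1. Add an event-ascertainment row to the participant timeline at 6 and 12 months, covering the four Table 3 events.
2. Ask identical, fixed questions in both arms within the household tablet survey that ASHA workers already carry out. Record the date of each event and obtain the hospital record where available. Where the participant has died, put the questions to the household.
3. Have the harms section refer to this procedure, so that Table 3, the timeline and the harms text agree.
4. Report events by the arm to which the cluster was allocated.
5. Align the bodies named in the harms section with item {5d}, either by describing the committee there or by naming only bodies that exist.
6. Optionally, record stroke as a separate event. While Table 3 and the timeline are being reconciled, PSQ-18 can be given a row as well.

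The cost is a few extra questions, a slightly longer interview and a small amendment. No extra visits or staff are needed. The trial status section expects the last inclusion in April 2026 after a February start, so on that timetable the first six-month contacts fall around August 2026. An amendment before then would avoid having to reconstruct midline events from recall.
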